**Figure 4 F4:**
[figure not shown]
**Telephone motivational interviewing protocol elements**. * Only in the third interview protocol of the TMI group and second interview protocol of the combined group

The protocols of the second, third and fourth interviews in the TMI group and of the second interview in the combined group contained an extra element after the introduction: Discuss progress on action plans, if plans were made, and discuss the current situation, if participants had no plans to change. This extra element was added to help participants make progress in changing their behavior or thinking about behavioral change. The interview protocols of the combined group contained an extra topic after the introduction: Discuss the tailored letter. The third protocol of the TMI group and the second of the combined group also contained the possibility for the interviewers to use the values clarification strategy described by Resnicow et al. [77].

Besides the interview protocols, interviewers received general information about cardiovascular diseases, hypertension and the specific health behaviors (physical activity, fruit and vegetable consumption and fat intake), and an MI-Change Talk card on which methods to evoke and strengthen change talk and confidence talk were summarized as described by Miller and Rollnick [42].

The TMIs were expected to take on average 20 minutes. The interviewers wrote a summary of each interview to assist in the next interview. Interviewers were scheduled to interview the same participants as far as possible; however, due to job transfers and availability, this was not always possible. To assess the interviewers' competence in the use of MI, the interviews were computer recorded. A random 20-minute segment of a random sample of 20% of the interviews will be coded, 20% of these (4% of all interviews) will be examined by two trained coders for inter-coder reliability with the use of the Motivational Interviewing Treatment Integrity (MITI 3.0) code [79,80] and the 1-PASS Coding System for Motivational Interviewing (1-PASS) [76]. The MITI 3.0 consists of two components: global scores and behavior counts. The global scores of empathy, MI spirit (evocation, collaboration and autonomy support) and direction capture an overall impression of the interview (1 = poor, to 5 = ideal), whereas the behavior counts examine specific interviewer behavior; the number of open and closed questions, simple and complex reflections, the provision of information, and MI adherent and non-adherent utterances. Recommended competency thresholds as described in the MITI 3.0 [80,81] will be used to determine interviewer competency for the behavior counts as well as the global scores. The 1-PASS consists of 16 items (1 = poor/never to 7 = excellent/always) that measure, for example, whether the interviewer effectively uses the importance ruler or values clarification strategy. The average 1-PASS score is calculated by dividing the sum of the items by the number of applicable items. As described in the 1-PASS manual, an average score of 5 is regarded as sufficient [76].

#### Tailored print communication versus telephone motivational interviewing

Because TPC and TMI are different methods, they are also expected to have different effects. The first reason for this stems from their media differences. TPC is print-based and essentially a passive, one-way form of communication. It is therefore assumed to have less impact on people with a lower education level [25], whereas TMI is more interactive and assumed to be more effective for these people. The second reason concerns individuals' motivation to change behaviors. The Protection Motivation Theory [82,83] states that people can be motivated to protect their health by two processes: threat appraisal and coping appraisal. Threat appraisal is influenced by individuals' perceived seriousness of the situation and their susceptibility. A higher perceived threat may lead to more motivation to protect oneself. In line with Protection Motivation Theory, people without hypertension are assumed to have less interest in and motivation to change than people with hypertension. Since people less ready to change may benefit more from motivation-enhancing interventions [48,84,85] it is possible, therefore, that people without hypertension will benefit more from TMI, because they may be more ambivalent and less ready to follow advice than people with hypertension. The largest effect is anticipated for the combined (TPC+TMI) group, as we assume that the positive aspects of both TPC and TMI will be reinforced in this group.

#### Hypotheses

Effect size estimates for our intervention and control conditions were difficult to determine, because similar studies were not available at the start of Vitalum (2003). However, one study on MI [48] and others on computer tailoring [27,33,40] found increases of at least 10% in one or more of the target behaviors (i.e., PA, fruit or vegetable consumption, or saturated fat intake) in participants who received single or multiple MI or tailoring compared to control group participants. As PA and fruit and vegetable consumption will receive more attention than saturated fat intake, we also expect to find larger effects for these. Therefore, we formulated the following hypotheses:

1. Compared to those in the control group, participants receiving either TMI or TPC will (a) increase PA as well as fruit and vegetable intake by 10% at the first follow-up from the expected mean at baseline; and (b) decrease saturated fat intake by 5%.

2. Participants receiving TPC+TMI will have resulting behavioral changes which exceed the sum of the changes expected given each intervention.

3. Participants with a low education level benefit more from TMI than TPC.

4. Participants without hypertension benefit more from TMI than TPC.

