3. The combined group (TPC+TMI), in which participants received two tailored print letters and two telephone motivational interviews in turns. The first letter and call addressed PA; the second letter and call focused on fruit and vegetable consumption. Participants could also choose to discuss fat intake in the fourth call. The total number of intervention components (4) was kept to a similar total number as that of the first two groups. Also, we exposed participants to an equal amount of each intervention type (2*TPC, 2*TMI) to keep the influence of both methods as comparable as possible.

4. The control group, in which participants received one tailored letter based on the last follow-up questionnaire.

Participants from the three intervention groups received their four intervention components at 5, 13, 30 and 43 weeks after they had returned the baseline questionnaire. This timeframe was chosen to spread delivery of the components throughout the year [48]. Vitalum used a two-way design (TMI * TPC) except for the fact that the combined group received half of each treatment type (2*TPC and 2*TMI instead of 4*TMI and 4*TPC). The study design and timeline is depicted in Figure 2.

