### Statistical analyses

#### Sample size and power

The required sample size was determined using the formula for unpaired *t*-tests [114], as each effect test in a balanced 2 × 2 between-subject design (i.e., the TMI and the TPC main effects and their interaction) comes down to such *t*-tests (apart from having less residual variance). The sample size calculation was based on the following assumptions: (a) since results of similar studies were not available at the start of Vitalum, the sample size calculation was based on a small expected effect size (Cohen's d) of .3 [115]; (b) a power of .9; (c) an alpha of .01 to correct for multiple testing; (d) an intra class correlation of .02, where the correlation is based on random treatment by GP interaction (a random GP main effect does not affect the sample size in the event of person randomizations within GPs) [116]; and (e) an expected average number of participants per general practice of 70. Loss of power due to random dropout or a gain in power from including the pretest as a covariate in the analyses [117] was not taken into account in the sample size calculation. However, the loss of power due to 20% random dropout can be compensated by including the pretest as a covariate if it correlates .5 with the posttest – the latter correlation being a realistic assumption. These assumptions resulted in a required sample size at baseline of 1,600. Thus, Vitalum aims to assess 400 participants per group at baseline. Assuming 50% of people refuse participation, and 40% of the remaining group meet the recommendations for PA and nutrition and are thus excluded, at least 5,400 people must be invited to secure 1,600 for the study.

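### The sample size covers the TMI × TPC interaction only for a departure of about 0.6 SD, and Hypothesis 2 sets an arm with half of each method against the sum of both

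*Protocol article*

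**What the plan says.** Under Hypotheses, the second hypothesis is one of super-additivity: "Participants receiving TPC+TMI will have resulting behavioral changes which exceed the sum of the changes expected given each intervention".

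Under Study design, after the list of the four groups, the article says: "Vitalum used a two-way design (TMI * TPC) except for the fact that the combined group received half of each treatment type". The single-method groups had four letters or four calls. The combined group had two of each, so that every active group had four contacts.

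Sample size and power bases the calculation on the unpaired t-test, on the ground that this is what "each effect test in a balanced 2 × 2 between-subject design (i.e., the TMI and the TPC main effects and their interaction" comes down to. The inputs are a Cohen's d of 0.3, power .9, "an alpha of .01 to correct for multiple testing", "an intra class correlation of .02, where the correlation is based on random treatment by GP interaction", and 70 participants per practice. The result is 1,600, or 400 per group.

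The section on primary and secondary outcome analyses enters intervention group as an independent variable and names no contrast for Hypothesis 2. The Discussion counts among the strengths that each single method is compared with the combined group.

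**The concern.** The sample size section speaks of the two main effects and the interaction in one breath, with one effect size. A reader will take it that the trial has 90% power for an interaction of 0.3 SD in the usual sense, that is, for a combined effect 0.3 SD above the sum of the single effects. It does not.

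Separately, the combined group is not the cell of a 2 × 2 design in which both methods are given in full. Its contacts match those of the single-method groups in number, so a sum of the two single-method effects is not its natural benchmark. The article discloses the halving under Study design, but neither the hypothesis nor the power section allows for it.

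At stake is one of four prespecified hypotheses. The article expects its results to guide policymakers, who could take a failed Hypothesis 2 as evidence against combining the methods when the benchmark and the low power may explain it.

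**Working it through.** **Inputs from the article.** d = 0.3; power .9; alpha .01; intraclass correlation .02; 70 per practice; 400 per group. Sidedness is not stated; two-sided is used because it reproduces the stated figure.

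**Step 1: reproduce the 1,600.**
- n per side = 2 × ((2.576 + 1.282)/0.3)² = 330.7, so 331, or 662 in total.
- Design effect = 1 + 69 × .02 = 2.38.
- 662 × 2.38 = 1,576, close to the stated 1,600. One-sided testing gives 580 × 2.38 = 1,380, which does not match.

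The match requires 800 v 800, so each test uses a margin of the 2 × 2 table.

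**Step 2: what d = 0.3 means for the interaction.** As an 800 v 800 t-test, the interaction compares the average of combined and control with the average of TPC and TMI. That difference is half the departure from additivity, D = combined − TPC − TMI + control. So d = 0.3 corresponds to D = 0.6 SD.

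**Step 3: power for D = 0.3 SD.**
- SE(D) = √(4 × 2.38/400) = 0.1543 SD.
- Power = Φ(0.3/0.1543 − 2.576) = Φ(−0.63) = 26.4%.
- For D = 0.6 the same formula gives 90.5%, equal to the power for a main effect of 0.3.
- Departure detectable with 90% power: 3.857 × 0.1543 = 0.595 SD.
- For 90% power at D = 0.3: 4 × 1,576, about 6,300 participants.

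Sensitivity of the 26.4%:

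| Variation | Power for D = 0.3 |
|---|---|
| The 1,629 actually randomized | 27.0% |
| One-sided alpha .01 | 35.1% |
| 20% dropout, pretest correlation .5 | 28.5% |
| 20% dropout, no covariate | 20.1% |
| Design effect 1.68 (assumes 35 per practice) | 39.7% |

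The design effect of 1.68 does not reproduce the stated sample size: 662 × 1.68 = 1,112.

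On the baseline SDs in Table 1, 0.6 SD is 0.6 × 3.8 = 2.3 hours a week of activity (49% of the mean of 4.7), 0.6 × 1.6 = 0.96 pieces of fruit (46% of 2.1), or 0.6 × 82.4 = 49 g of vegetables (30% of 165.2). That is the required excess above the sum. Hypothesis 1 expects 10% per method.

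**Step 4: the effect of halving.** The article gives no relation between number of contacts and effect, so this step rests on assumption. Let each four-contact method gain 0.3 SD, and let half of each method keep a given share of that gain. The synergy column adds a true 0.3 SD to the combined group. The last column uses the SE from step 3.

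| Share kept | D, no synergy | D, synergy 0.3 | Chance of a significant positive D with synergy |
|---|---|---|---|
| 50% (proportional) | −0.30 | 0 | 0.5% |
| 75% | −0.15 | +0.15 | 5.4% |
| 100% | 0 | +0.30 | 26.4% |

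**Step 5: a comparison at equal contacts.** Combined minus the average of TPC and TMI has SE = √((1/400 + 1/800) × 2.38) = 0.0945. Power for 0.3 SD is Φ(3.176 − 2.576) = 73% (89% at design effect 1.68). Combined v control has SE = √(2 × 2.38/400) = 0.109, and power for 0.3 SD is 57%.

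**The case against.** Much can be said for the article. It is algebraically right that the interaction reduces to an unpaired t-test, and it nowhere claims power for a 0.3 SD departure. The 1,600 is correct for main effects of 0.3 SD. The halving is stated openly. These points stand. They leave the missing translation of d for the interaction and the mismatch between benchmark and arm.

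Several stronger readings are tempting, and the documents do not support them:

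- *That the halving causes the low power.* It does not. Step 3 contains no assumption about contacts.
- *That the test is biased against synergy as a matter of fact.* If Hypothesis 2 means the sum of the two four-contact effects, the contrast is unbiased for that statement, though it is a stricter target than synergy. The hypothesis does not say how many contacts its sum refers to. The shift also vanishes if half of each method keeps its full effect.
- *That the plan will probably report antagonism.* The analysis section fixes no contrast; the link to the interaction comes from the design description and the power section. Even at D = −0.30, a significant negative result has only about a 26% chance.
- *That the trial could not show that combining is better.* The Discussion announces direct comparisons of each single method with the combined group.

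The equal-contact contrast has a limit of its own. It has expectation zero without synergy only if effects are proportional to contacts. At 75% retention the combined group would reach 0.45 SD against an average of 0.30, an advantage of 0.15 SD without synergy, which would be significant in about 16% of trials.

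**Conclusion.** The point holds as two independent findings.

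(1) The power statement does not carry over to the interaction in the sense most readers will give it. It covers a departure of about 0.6 SD. Power for 0.3 SD is about 26%, on the article's own alpha, sample size and design effect, with two-sided testing assumed.

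(2) The benchmark in Hypothesis 2 does not fit the arm. The direction of the shift needs only that two contacts achieve less than four. Its size, 0 to −0.30 SD, rests on an assumed 0.3 SD per single method and an assumed range of retention. A null or negative interaction is therefore not evidence of absent synergy or of antagonism.

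Neither finding touches the 1,600 as a figure for main effects of 0.3 SD.

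**What to change.** 1. In Sample size and power, limit the 90% statement to main effects of 0.3 SD, and add that for the interaction it covers a departure from additivity of about 0.6 SD, with about 26% power at 0.3 SD.
2. At Hypothesis 2, say which number of contacts the sum refers to. State that, because the combined group received half of each method, a null or negative interaction cannot be read as absence of synergy or as antagonism.
3. Prespecify as the main test for the combined group the contrast combined minus the average of TPC and TMI, together with combined v control. Word a positive first contrast as better at an equal number of contacts. This makes explicit a comparison that the Discussion already implies.
4. Keep the super-additivity contrast, if at all, as exploratory, with its confidence interval.

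The cost is one reworded hypothesis, one named contrast and one corrected sentence on power. Neither the groups nor the sample changes. The trial gives up a confirmatory claim of super-additivity.

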### Outcome measures

#### Primary outcome measures

To measure the efficacy of TPC, TMI and TMI+TPC, the primary outcome measures of Vitalum were PA, fruit and vegetable consumption and whether participants adhered to public health guidelines with regard to these behaviors. These were measured at baseline, the intermediate telephone survey and both follow-ups (25, 47 and 73 weeks after baseline respectively). Since PA and fruit and vegetable consumption receive more attention in Vitalum, saturated fat intake was seen as a secondary outcome measure. Other studies showed that multiple-item measurements may result in people overestimating their behavior [86-95] and that adjusting the results of a multiple-item measurement with those of a single-item measurement let to reduced overestimation [86-88,92,93]. Therefore, the primary outcome measures are single – as well as multiple-item measurements, and both are combined into a measure as described below to reduce overestimation.

##### Physical activity (PA): single-item measurement

PA was assessed using one item, the final question of the Short Questionnaire to Assess Health-enhancing physical activity (SQUASH) [96]: "How many days a week do you cycle, engage in do-it-yourself (DIY) activities, do gardening, play a sport or engage in other strenuous physical activities for at least 30 minutes a day?" The SQUASH has been validated with an accelerometer (CSA activity monitor, *r*_*spearman *_= .45, *p *< .01). In terms of the single-item adherence measurement, participants were classified as adhering to the Dutch PA guideline if their answer to this question was 5 or more days [7,11,13].

##### Multiple-item measurement

PA was also measured using 28 items from the modified CHAMPS physical activity questionnaire [97], which assesses the frequency of an activity (times per week) and its duration (hours per week). This questionnaire has been validated with cardiorespiratory fitness (VO_2 _maximum) estimated by a submaximal treadmill test (*r*_*pearson *_= .17, *p *< .05) [97]. Activities that were measured included: walking leisurely; walking fast or briskly; cycling leisurely; cycling fast or briskly; doing light gardening; doing heavy gardening; doing light housekeeping; doing heavy housekeeping; jogging or running; swimming; playing tennis, table tennis or badminton; playing a team sport indoors or outdoors; doing light exercises to maintain a physical condition, for example, stretching or flexibility exercises; and doing heavy exercises, for example aerobics, fitness or strength training. Metabolic equivalents (METs) were determined for each activity on the basis of the PA compendium by Ainsworth et al. [98]. MET levels were used as cut-offs to calculate the total number of weekly PA hours with at least a moderate intensity. Only activities with at least four METs were considered moderate for participants younger than 55, and activities with at least three METs considered moderate for participants aged 55 and older [11]. In terms of multiple-item adherence measurement, participants were classified as adhering to the PA guideline if they were physically active with at least moderate intensity for at least 2.5 hours a week.

##### Combined measure

Multiple- and single-item measurements were also recoded into a combined measure to classify adherence: participants were only coded as "meeting the PA guideline" if they did so according to both the multiple- and single-item measurements.

##### Fruit and vegetable consumption: single-item measurement

Both fruit and vegetable consumption were assessed using single-item measurements: one for fruit ("How many days a week do you eat at least two pieces of fruit?") and one for vegetables ("How many days a week do you eat at least 200 g of vegetables?"). In terms of the single-item adherence measurement, participants were classified as adhering to the guideline for fruit and vegetable consumption if their answer to both these questions was 7 days [10].

##### Multiple-item measurement

Fruit and vegetable consumption was also measured using 16 items from the short questionnaire for fruit and vegetable intake [99]. The questionnaire has been validated with blood levels of carotenoids (*r*_*spearman *_= .39, *p *< .001 for fruit; *r*_*spearman *_= .24, *p *< .001 for vegetables) and vitamin C (*r*_*spearman *_= .37, *p *< .001 for fruit; *r*_*spearman *_= .26, *p *< .001 for vegetables) [99]. This questionnaire measured frequency (days per week) and quantity (pieces/serving spoons per day) of vegetables (cooked and raw) and fruit (fruit juice, citrus fruits, tangerines, apples or pears, bananas and other fruits). Two tangerines were considered one piece of fruit. Frequency and quantity were used to determine daily consumption. In terms of the multiple-item adherence measurement, participants adhered to the fruit consumption guideline if they consumed at least two pieces (two servings) a day, and to the vegetable consumption guideline if they consumed at least 200 g (4 serving spoons) a day [10].

##### Combined measure

Multiple- and single-item measurements were recoded into a combined measure to classify adherence: participants were only coded as "meeting the fruit guideline" if they did so according to multiple- and single-item measurements. The same applied for vegetable consumption.

#### Secondary outcome measures

Secondary outcomes include saturated fat intake, health-related quality of life, body mass index (BMI) and cognitive behavioral determinants. Except the latter, these were measured at baseline and both follow-ups (43 and 73 weeks after baseline). Cognitive determinants of primary behavioral outcomes were also measured at the first telephone survey (25 weeks after baseline); but because Vitalum's main focus was to measure behavior change, cognitive behavioral determinants of all outcomes – except for intention – were not measured at the second follow-up (73 weeks after baseline). This also reduced the length of the second follow-up questionnaire, thereby possibly reducing dropout.

*Saturated fat intake *was measured using a 35-item short food frequency questionnaire, the Fat list [100]. The list has been validated with a 7-day diet record (*r*_*pearson *_= .69 for saturated fat intake, *p *not reported) [100]. Saturated fat intake was assessed using questions about frequency and quantity of 19 food items (dairy products, bread spreads, cheese, meat, gravy, savory snacks and sweet snacks). Frequency, quantity and item type were used to calculate a total fat score for the 19 items (0–5 points per item). One fat point represents about 2 g of saturated fat intake. Respondents were classified as adhering to the guideline for saturated fat intake depending on gender: men with a total fat score of 15 or less and women with 13 or less [100].

*Health-related quality of life *was measured with the RAND 36-item Health Survey 1.0 [101,102] which measures individuals' physical and social functioning, role limitations due to physical or emotional problems, mental health, pain, general health perception and health change.

*BMI *was calculated from self-reported body weight and height (kg/m^2^).

*Cognitive behavioral determinants *were measured using variables that represent the I-Change Model [69-71]. Behavioral determinants were measured for each behavior, fruit and vegetable consumption separately, and included stages of change [103,104], attitudes [30], social influence [30], self-efficacy expectations [105], ability factors (i.e., action plans) [106], habit [107], and awareness based on self-rated behavior and the assessment of behavior by questionnaire [108,109]. These questions were also based on previous questionnaires (see references for each construct) as well as unpublished results of focus group interviews with people from the study population. The baseline questionnaire was piloted for comprehension and conceptual salience with representatives of the study population.

